**S1. Study Protocol**

**Kisel-10- a prospective randomized double-blind placebo controlled study of the results of intervention with selenium and coenzyme Q10 combined, regarding effect with emphasis on cardiovascular mortality and morbidity.**

**Background**

The amount of patients suffering from heart failure is increasing throughout the Western hemisphere. The prognosis of heart failure is poor, in many cases worse than malignant diseases.

Several studies have demonstrated that by evaluating the plasma concentration of the natriuretic peptides that are stimulated by increased wall tension of the myocardium, it is possible to estimate the risk of cardiovascular mortality.

Scientific reports have demonstrated decreased symptoms of heart failure after selenium supplementation. Selenium, which is acquired by the body through food, often exists in low levels in the body in the northern parts of Europe due to low levels of selenium in the soil. Animal studies have shown that selenium has a positive effect on the myocardium.

Ubiquinon, commonly called Q10, has a central position in many of the enzyme systems of the body. It has recently been shown that the body requires the presence of Q10 to produce selenium containing enzymes which are central in the energy handling processes of cells.

During the study all participants will be followed-up with blood samples, a new patient record, and new tablets every six months. Evaluation of health related quality of life will be performed at inclusion, after 18 months and after 48 months. The quality of life will be evaluated using the validated instrument SF-36. At the end of the study, new blood samples and new echocardiograms will be obtained.

**Aim**

To evaluate changes in primarily cardiovascular mortality and all-cause mortality, and secondary, cardiac function as evaluated with cardiac natriuretic peptides and echocardiography after dietary supplementation of selenium and Q10, or a placebo, in an elderly population during 48 months of intervention.

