**Endpoint**

Development of cardiovascular disease, worsening of existing cardiovascular disease, and cardiovascular mortality during intervention with selenium and Q10 in comparison with placebo.

Change of concentration of natriuretic peptides during intervention with selenium and Q10.

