**Secondary endpoint**

Development of all-cause mortality during intervention with selenium and Q10.

Consumption of hospital resources during intervention with selenium and Q10 in relation to placebo.

To evaluate possible mechanisms of interventions as seen in blood samples if effects could be demonstrated as described in the primary endpoint.

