**Basic power calculation**

Using the assumption that the incidence of occurrences in the placebo group during a follow up of 4 years is 40%, and 28% in the intervention group, i.e. a difference in incidence between the groups of 30% and an absolute difference of 12%, 244 individuals are needed in order to obtain a statistical power of 80% with a significance level of 5%. A dropout frequency of 15% is to be expected, which is why a minimum of 560 individuals is needed in order to obtain significant differences.

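### The protocol's Aim and its endpoint sections disagree on which outcome is primary, and the power calculation does not settle it

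*Protocol*

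**What the plan says.** Four sections of the protocol bear on the primary outcome.

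- **Aim.** The trial is "To evaluate changes in primarily cardiovascular mortality and all-cause mortality, and secondary, cardiac function as evaluated with cardiac natriuretic peptides and echocardiography". Two mortality outcomes come first; peptides and echocardiography come second.
- **Endpoint.** There are two entries. The first is "Development of cardiovascular disease, worsening of existing cardiovascular disease, and cardiovascular mortality during intervention with selenium and Q10 in comparison with placebo". The second is "Change of concentration of natriuretic peptides during intervention with selenium and Q10". The heading does not contain the word primary.
- **Secondary endpoint.** The first entry is "Development of all-cause mortality during intervention with selenium and Q10". A later entry makes the study of mechanisms conditional: "if effects could be demonstrated as described in the primary endpoint".
- **Basic power calculation.** One comparison is sized, 40% against 28% over four years, "in order to obtain a statistical power of 80% with a significance level of 5" per cent. The event counted is called only an occurrence; no outcome is named.

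**The concern.** Two outcomes change rank between sections. All-cause mortality is primary in the Aim and secondary in the endpoint sections. Natriuretic peptides are secondary in the Aim and stand under Endpoint. Cardiovascular mortality has top rank in both places, but on its own in the Aim and in one entry with new and worsening disease in the Endpoint section. Cardiovascular morbidity is absent from the Aim altogether.

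This goes beyond an aim being broader than its endpoint, because the order of named outcomes is reversed. Nor can it be left to a statistical analysis plan: a plan that followed one section would contradict another. What is at stake is the freedom to decide, once results are known, which outcome was primary, and to cite protocol text for the choice. The mechanism objective inherits the ambiguity, because its condition refers to a primary endpoint in the singular while the Endpoint section has two entries.

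**Working it through.** **1. Rank of each outcome, side by side**

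| Outcome | Aim | Endpoint / Secondary endpoint |
|---|---|---|
| Cardiovascular mortality alone | primary | not listed alone (part of the first Endpoint entry) |
| All-cause mortality | primary | secondary |
| New or worsening cardiovascular disease with cardiovascular mortality | not listed | Endpoint |
| Natriuretic peptides | secondary | Endpoint |

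Four distinct outcomes hold top rank in one place or the other, if the first Endpoint entry is one composite. Counting its items separately gives five: cardiovascular mortality, all-cause mortality, new disease, worsening disease and peptides.

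**2. Does the power calculation decide it?** Inputs from the protocol: p1 = 0.40, p2 = 0.28, power 80%, level 5%. Assumed: two-sided test, 1:1 allocation. With mean rate p = 0.34,

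n per arm = [1.960·√(2·0.34·0.66) + 0.842·√(0.40·0.60 + 0.28·0.72)]² / 0.12² = 243.4, rounded up to 244.

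This reproduces the stated 244 as a per-arm figure, so 488 in total. Allowing for 15% dropout, 488 × 1.15 = 561 and 488 / 0.85 = 574.1, rounded up to 575; both are close to the stated 560. The arithmetic is sound for one outcome at 5%, but that outcome is not named.

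The choice matters for power. If the same 30% relative reduction applied to a mortality outcome with a placebo rate of 10% to 20% (assumed; the protocol gives no mortality rate), power at 244 per arm would be about 22% to 42% instead of 80%.

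**3. False-positive chance if each candidate were tested at 5% (assumed)**

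Under independence:
- two outcomes: 1 − 0.95² = 9.75%
- four outcomes: 1 − 0.95⁴ = 18.5%

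The outcomes overlap, because cardiovascular death is contained in all-cause death and in the composite, so the true figures are lower. A simulation with no treatment effect used 280 per arm (560 / 2) and assumed rates of 10% for cardiovascular death, 16% for all-cause death and 40% for the composite, with peptide change unrelated to events:
- Aim's pair: about 8%
- Endpoint section's pair: about 10%
- all four: about 16% to 17%

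Varying the assumptions (cardiovascular death 5% to 20%, all-cause death 12% to 25%, composite 20% to 40%, peptides unrelated or related to events) gives about 12% to 18% across all four. The low end arises when peptides correlate with events, a link that the protocol's Background itself describes for cardiovascular mortality. As a cruder check, four equally correlated normal statistics give about 17%, 16%, 13% and 9% at correlations of 0.3, 0.5, 0.7 and 0.9. Even the extreme case stays above 5%.

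**4. If all four were kept as primary.** With a Bonferroni level of 0.05 / 4 = 0.0125, 40% against 28% needs 347 per arm. That is 694 in total, and 694 / 0.85 = 817 after dropout. At 244 per arm, power falls from 80% to 62%.

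**The case against.** Several parts of the opposing case stand.

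- **Testing level.** A reader might infer that the protocol tests four primary outcomes, each at 5%, and so runs an error rate of 16% or more. It does not say that. The 5% appears once, in the power calculation, and is assigned to no list of outcomes. A rule for multiplicity may sit in a statistical analysis plan that is not at hand, so its absence from the protocol is no fault.
- **Rank of the peptides.** That peptides are primary in the Endpoint section is inferred from its position opposite the Secondary endpoint section and from that section's reference back to a primary endpoint. The reference is singular and could mean the first entry only. The reversal for all-cause mortality needs no such inference on its secondary side, which is explicit.
- **Pooling.** The four-outcome figure combines two conflicting accounts. On the composite reading, each account alone names two outcomes.
- **Planning rates.** It is tempting to say that 40% and 28% must belong to the composite. The protocol gives no event rate by outcome, so it does not support this.
- **Mechanism objective.** Its condition is ambiguous between two entries; it is not missing.

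None of this removes the conflict over all-cause mortality between the Aim and the Secondary endpoint section, which nothing else in the protocol resolves.

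**Conclusion.** The protocol contradicts itself on its primary outcome, and this needs correcting. The finding rests on the wording of the Aim, Endpoint and Secondary endpoint sections and on the unnamed event in the power calculation. It does not rest on a missing multiplicity adjustment. The error rates above show what could follow; they hold only if every candidate is tested at 5%, and the four-outcome range only if someone chooses across both accounts. The event rates and correlations behind them are assumed, so the ranges should be quoted and not a single value. The sample size arithmetic is not at fault.

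**What to change.** Before unblinding:

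1. Name one primary outcome and word it identically in the Aim, Endpoint, Secondary endpoint and Basic power calculation sections.
2. State whether the first Endpoint entry is a single composite.
3. State that the 40% and 28% rates refer to the chosen outcome. If they do not, redo the calculation with rates that do.
4. Rank every other outcome as secondary.

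The composite of new or worsening cardiovascular disease or cardiovascular death is one reasonable choice, since it fits the title and the Endpoint section. It would need an event definition for worsening, which the protocol lacks. The choice of outcome, and any order of testing, belong to the sponsor.

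The cost is mainly wording, plus that definition if the composite is chosen. With one primary outcome at 5%, 244 per arm still applies provided the planning rates belong to it. The downside is small: outcomes not chosen can no longer be claimed as primary successes.

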**Secondary objectives**

To evaluate the cost-effectiveness of selenium and Q10 combined during an intervention of 48 months. To measure the perceived health related quality of life during intervention.

Possible health related economic consequences will be evaluated using the instrument EQ-5D.

**Endpoint**

Development of cardiovascular disease, worsening of existing cardiovascular disease, and cardiovascular mortality during intervention with selenium and Q10 in comparison with placebo.

Change of concentration of natriuretic peptides during intervention with selenium and Q10.

**Secondary endpoint**

Development of all-cause mortality during intervention with selenium and Q10.

Consumption of hospital resources during intervention with selenium and Q10 in relation to placebo.

To evaluate possible mechanisms of interventions as seen in blood samples if effects could be demonstrated as described in the primary endpoint.

**Study design**

A prospective randomized double-blind placebo controlled study.

**Randomizing**

The randomising procedure will be performed using PharmaNord’s computer assisted randomization in blocks of 6.

**Study**

All participants will be offered a selenium-containing yeast preparation corresponding to 200 micrograms of selenium/day, and ubiquinone corresponding to 200 milligrams/day, or a placebo.

During the intervention period, blood samples will be drawn every six months from all participants, and the following list of substances are to be analyzed:

1. NT-proBNP
2. Thioredoxin
3. Thioredoxinreductase
4. Lipidperoxidase
5. Panel of cytokines
6. “New” biomarkers for heart failure
7. Panels of biomarkers for inflammation, oxidative stress, and ischemia.

All blood sample results will be blinded for both the investigators and the participants.

**Inclusion criteria**

Individuals living in the municipality of Kinda, aged between 70-80 years who have accepted participation in the study, and who are expected to fulfill a study period of 4 years.

**Exclusion criteria**

Recent myocardial infarction (within 4 weeks).

Planned cardio-vascular operative procedure within 4 weeks.

Hesitation concerning if the candidate can decide for him/herself whether to participate in the study or not, or if he/she understands the consequences of participation.

Serious disease that substantially reduces survival or where it is not expected that the participant can cooperate for the full 4 year period.

Other factors making participation unreasonable, such as long/complicated transport to the Primary Health Center where the project is managed, or drug/alcohol abuse.

**Preparations**

Coenzyme Q10 ( Bio-Quinon 200mg, PharmaNord, Vejle, Denmark)

Selenium (SelenoPrecise 200 microgram, PharmaNord, Vejle, Denmark)

Placebo (PharmaNord, Vejle, Denmark)

All preparations will be ingested twice a day together with food.

The preparations will be supplied by PharmaNord, Vejle, Denmark. The preparations will be stored in a locked, dry, dark room where only the personnel involved in the study will have access. A rigorous log regarding received and delivered preparations will be kept.

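### The Preparations section, read as unit strengths taken twice a day, gives double the daily dose in the Study section, and the protocol does not say how the two agree

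*Protocol*

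**What the plan says.** The Study section is the only place that states a daily dose. Active participants are offered a "selenium-containing yeast preparation corresponding to 200 micrograms of selenium/day", together with "ubiquinone corresponding to 200 milligrams/day". Both figures are totals per day.

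The Preparations section identifies the products as "Bio-Quinon 200mg, PharmaNord, Vejle, Denmark" for Q10 and "SelenoPrecise 200 microgram, PharmaNord, Vejle, Denmark" for selenium, followed by a placebo from the same manufacturer. It then gives one frequency for everything: "All preparations will be ingested twice a day together with food". It does not give the content of a single tablet or capsule, the number of units per intake, or a daily total.

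The other sections do not fill the gap. The Background says that participants get new tablets at six-month intervals, but not how many. The Aim sets the intervention at 48 months.

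**The concern.** A strength attached to a product name is ordinarily taken as the content of one unit. A reader who does so here, and applies the stated frequency, reaches twice the daily dose in the Study section. Nothing else in the protocol corrects that reading.

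The dose is the intervention under test, so the ambiguity bears on three things.

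- **What the result applies to.** An effect, or its absence, should be attributable to one known daily exposure. With two readings available, the protocol does not fix that exposure.
- **Safety.** The population is aged 70 to 80 and includes people under treatment for various diseases. The section on concomitant treatment foresees some on warfarin and recommends an INR check. The Dropouts section treats selenium or Q10 taken outside the study as grounds for counting a participant as a dropout, so the protocol itself regards extra exposure as material.
- **Detection.** The list of blood analytes in the Study section names neither selenium nor Q10 concentration. All blood results are blinded to investigators and participants, and the allocation code is sealed. A departure from the intended dose might not come to light during the trial, so the written dosing instruction carries much of the burden.

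**Working it through.** **Inputs**

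- Stated daily total (Study): 200 micrograms of selenium and 200 mg of Q10.
- Figure in the product designation (Preparations): 200 micrograms and 200 mg.
- Intakes per day (Preparations): 2, for all preparations.
- Content of one unit and units per intake: not stated.

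**Formula**

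Daily dose = strength per unit x units per intake x intakes per day.

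Two of the four quantities are given: the daily dose (Study) and the intakes per day (Preparations). The other two must be assumed, so I tried both natural readings.

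**Reading A: the designation is the strength of one unit, with one unit per intake**

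- Selenium: 200 x 1 x 2 = 400 micrograms per day.
- Q10: 200 x 1 x 2 = 400 mg per day.
- Ratio to the Study section: 400 / 200 = 2.0 for each component.

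The stated daily total is not reproduced.

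**Reading B: the designation is the daily total, split over two intakes**

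- Needed per intake: 200 / 2 = 100 micrograms of selenium and 100 mg of Q10.
- Daily total: 100 x 2 = 200 of each.

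The stated daily total is reproduced, but only with amounts per intake of 100 micrograms and 100 mg, which appear nowhere in the protocol.

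**Consequence for the supply log**

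Half a year is 365 / 2 = 182.5 days. If the units are of the labelled strength, a daily total of 200 means one unit per day, about 183 units of each product per participant per six-month issue. Two units per day means 365. The protocol requires a log of preparations received and delivered, but without a figure for units per intake it gives no expected count to check that log against.

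**What is not affected**

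No dose enters the power calculation, so the sample size does not depend on this point. The frequency statement covers the placebo as well, so the ambiguity concerns the amount of active substance, not a difference in regimen between the arms.

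**The case against.** The strongest reply is that this is an ambiguity and not a proven contradiction. The Study section is the only statement of daily dose. The Preparations section gives product designations and a frequency; it never states 400 per day, 200 at each intake, or one unit per intake. The figure of 400 needs two assumptions, that the designation is a unit strength and that one whole unit is taken each time. If the designation is instead the daily amount, the two sections agree for both components. Pack contents and label directions, which would settle the matter, are not in the protocol.

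Most of this stands. The factor of two is conditional. A reader might infer that the protocol prescribes 400 micrograms and 400 mg per day, or that every active participant would receive double the Study dose for 48 months. The document supports neither inference: it gives no number of units to dispense and says nothing about what was packed or taken.

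The reply does not remove the problem. Agreement between the sections needs an assumption that the protocol does not state and that departs from the usual reading of a product strength. Dose, unit strength and units per intake belong in the protocol and are not details to be left to an analysis plan. The relevant sentences are complete, so the gap cannot be put down to a redaction or a broken table.

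**Conclusion.** The point holds as an internal inconsistency in the protocol as written; it is not a criticism of a design choice. With the product figures read as unit strengths and one unit per intake, the Preparations section gives 400 micrograms of selenium and 400 mg of Q10 per day against 200 and 200 in the Study section, a factor of 2.0 for each. With the figures read as daily totals split over two intakes, the factor is 1.0. The protocol does not say which reading applies, so staff could deliver up to twice the daily dose in the Study section.

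It is certain that unit strength and units per intake are not stated. The doubling depends on Reading A. No view is taken here on which dose is intended. Because the uncertainty concerns the tested exposure itself over 48 months, it should be settled even though the correction is small.

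**What to change.** Reconcile the Study and Preparations sections. For each product, state the strength of one unit, the units per intake, the intakes per day and the resulting daily total. The product of the first three should equal the fourth, and the daily total should be identical in both sections. Describe the placebo in the same terms (units per intake, intakes per day). Carry the same figures into the participant instructions and the supply log, so that an expected count per six-month issue can be checked. The sponsor and investigators must confirm which dose is intended.

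The cost is a few lines of protocol wording and a check against the product labels. The design, the sample size and the analysis do not change.

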**Concomitant pharmacological treatment**

Participants who have been prescribed pharmacological drugs due to concomitant diseases/medical conditions are advised to continue treatment.

Participants who have been prescribed anticoagulants containing warfarin are advised to continue treatment, but it is recommended that they analyze the INR at the start of the intervention with selenium and Q10, and again after 2 weeks. Interactions between selenium/Q10 and warfarin have been discussed in literature but have not been demonstrated.

**Where is the code list?**

The code list containing information of active treatment/placebo is kept in a sealed envelope at the University Hospital, Linköping, and the codes will not be broken before the end of the study, or in the case of an emergency where information regarding the intervention is required.

**Side effects**

Serious side effects should be reported to both the National Board of Health and Welfare and PharmaNord ApS, Denmark.

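### The protocol's only adverse-event reporting rule depends on judged causality, and nothing provides for recording non-fatal, non-cardiovascular serious events in both arms whatever the cause

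*Protocol*

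**What the plan says.** The Side effects section of the protocol is a single sentence: "Serious side effects should be reported to both the National Board of Health and Welfare and PharmaNord ApS, Denmark". It defines neither serious nor side effect, and it does not say who makes the judgement. It directs reports to an authority and to the supplier, and it mentions no record kept for comparison within the trial.

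Other sections bear on what is captured:

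- **Background:** all participants are "followed-up with blood samples, a new patient record, and new tablets every six months". The content of the patient record is not described, and no enquiry about adverse events is named.
- **Endpoint:** the clinical endpoint is "Development of cardiovascular disease, worsening of existing cardiovascular disease, and cardiovascular mortality during intervention with selenium and Q10 in comparison with placebo".
- **Secondary endpoint:** this section adds "Development of all-cause mortality during intervention with selenium and Q10" and "Consumption of hospital resources during intervention with selenium and Q10 in relation to placebo".
- **Concomitant pharmacological treatment:** for warfarin users, "it is recommended that they analyze the INR at the start of the intervention with selenium and Q10, and again after 2 weeks".
- **Where is the code list?:** the code may be broken "in the case of an emergency where information regarding the intervention is required".
- **Dropouts:** reasons for leaving are registered if the participant gives them.

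**The concern.** Calling something a side effect presupposes that the product caused it. This trial treats people aged 70 to 80, some already under treatment for other diseases, for 48 months under double blinding. In that setting a single new cancer, serious infection, fracture or case of diabetes can seldom be assigned to a food supplement, and the natural explanation is age or existing disease. An excess of such events would show in the comparison with placebo, not in case-by-case judgement. That comparison needs the events recorded in both arms by the same rule, whatever anyone thinks caused them.

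This is a matter for the protocol. An analysis plan can settle how events are tabulated, but it cannot be relied on to recover events that were never collected. At stake is whether a claimed cardiovascular benefit can be set against a sound comparison of non-fatal harm of other kinds. The efficacy comparison itself is not affected.

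**Working it through.** **Step 1. Which serious events have an assured count by arm?**

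| Type of serious event | Provision in the protocol | Depends on judged cause? |
|---|---|---|
| New or worsening cardiovascular disease, cardiovascular death | Endpoint, against placebo | No |
| Death from any cause | Secondary endpoint | No |
| Any event leading to hospital use | Secondary endpoint as resource use relative to placebo; not described as admissions by diagnosis | No, but non-diagnostic |
| Event leading to withdrawal | Dropout reason, if volunteered | No, but incomplete |
| Other non-fatal, non-cardiovascular serious event, by type | Side effects section only | Yes |

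The INR advice and emergency code-breaking are safety provisions, but neither captures events. The last row of the table is the gap. Resource use fills it only in part: a rise in admissions for one diagnosis could be offset in the total by a fall in cardiovascular admissions, which is what the trial hopes to see.

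**Step 2. The trial's size.** The Basic power calculation section assumes 40% against 28% over four years, 80% power and a 5% level, and gives 244. With p̄ = 0.34, two-sided:

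n = [1.96 √(2 × 0.34 × 0.66) + 0.8416 √(0.40 × 0.60 + 0.28 × 0.72)]² / 0.12² = (1.3131 + 0.5593)² / 0.0144 = 243.4, so 244 per arm.

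The stated figure is reproduced as a per-arm number. Two arms need 488. Allowing for 15% dropout gives 488 × 1.15 = 562 or 488 / 0.85 = 575, both within 3% of the stated minimum of 560. Allocation is not stated. Assuming 1:1, 560 gives 280 per arm. None of these figures concerns safety; they only fix n for the next step.

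**Step 3. Illustration of what recording all events could show.** The protocol gives no rate for non-cardiovascular serious events and no attribution fraction, so every rate below is an assumption. With n = 280 per arm and a two-sided 5% level:

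power = Φ{ [ |p₁ − p₀| √n − 1.96 √(2p̄(1 − p̄)) ] / √(p₀(1 − p₀) + p₁(1 − p₁)) }

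For 10% against 20%: (1.6733 − 1.96 × 0.5050) / 0.5000 = 1.367, so power is 0.914.

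| All events counted: placebo v active | Expected participants with event | Power |
|---|---|---|
| 10% v 12.5% | 28 v 35 | 15% |
| 10% v 15% | 28 v 42 | 43% |
| 5% v 10% | 14 v 28 | 61% |
| 10% v 20% | 28 v 56 | 91% |

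**Step 4. The same 10% v 20% if only attributed events reach the count.** The same fraction is assumed to be attributed in each arm, as blinding would suggest.

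| Share attributed and reported | Rates seen | Expected reports | Power |
|---|---|---|---|
| 5% | 0.5% v 1.0% | 1.4 v 2.8 | 10% |
| 20% | 2% v 4% | 5.6 v 11.2 | 28% |
| 50% | 5% v 10% | 14 v 28 | 61% |

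The normal approximation is poor at the smallest counts. Fisher's exact test gives about 2% in the first row and about 21% in the second, so the approximation does not overstate the loss. With 238 per arm (560 × 0.85 = 476, halved) the corresponding powers are 87% with all events counted, and 9% and 25% at 5% and 20% attribution.

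**The case against.** Four points can be made for the protocol.

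1. **Much serious harm is already compared.** A reader might infer that the trial would make no valid comparison of harm, or that an excess of any common serious event would go uncompared. The documents do not support that. Cardiovascular events and deaths, among the commonest serious events at this age, are endpoints that need no attribution, and hospital use relative to placebo partly reflects other serious illness. This objection stands, and it limits the point to non-fatal, non-cardiovascular events.

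2. **A reporting rule is not a recording rule.** The Side effects section says where certain reports go. It does not forbid other recording, and the six-monthly patient record may well note intercurrent illness. To say that such events would never be counted goes too far. What remains is that the protocol does not provide for the count, so it is not assured.

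3. **Tabulation belongs elsewhere.** A by-arm safety table is commonly left to an analysis plan, and the content of the visit record to a case report form. Neither was at hand, and part of the protocol's own text was also unavailable. This stands for the table and the layout of the form. It does not answer the point about collection, because the one rule that the protocol does state turns on judged cause.

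4. **The power figures can flatter the case.** A doubling from 10% is favourable. With complete recording, 10% against 12.5% would still usually be missed. The contrast between counting all and only attributed events also supposes that unattributed events go unrecorded, which the protocol does not say. The figures are therefore an illustration over a range and estimate nothing about this product.

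A reader might also call this the only safety rule in the protocol. That is inexact, given the INR advice and the provision for emergency code-breaking. It is the only rule on reporting adverse events.

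**Conclusion.** The point holds in a limited form. The sole adverse-event reporting rule is triggered by a judgement of causality, and no section provides for recording non-fatal, non-cardiovascular serious events in both arms regardless of that judgement. An excess of such an event on active supplement could therefore be missed. It does not follow that harm goes uncompared altogether, since cardiovascular events and all deaths are compared without attribution and hospital use gives a partial signal.

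The size cannot be fixed from the protocol. Under the assumed rates, full recording would detect a doubling from 10% with good power but would have little chance against a modest excess. A count restricted to attributed events would lose most of the power even for the doubling if attribution were 20% or less. These figures rest on 1:1 allocation, 280 per arm, equal attribution in both arms and the assumed event rates.

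This should be corrected. It does not threaten the efficacy result, but it weakens any statement on safety that accompanies it.

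**What to change.** Amend the Side effects section in three respects:

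- Define serious, and state that all serious adverse events are recorded in both arms at each existing six-monthly contact, whatever their judged cause.
- State that these events are compared by randomised arm at the end of the trial. The form of the table can be left to the analysis plan.
- Keep the reporting of suspected serious side effects to the authority and the supplier as a separate step.

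The cost is one further item on the patient record already planned, a little more recording time and one table by arm. It adds no visits and leaves the preparations, the schedule and clinical management unchanged.
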